**Methods and outcomes:**

The CIPS-TER study is a 2-year prospective, single-blind, randomized clinical trial. One hundred patients with ischemic or hemorrhagic stroke will be enrolled in the study, within 5–21 days after onset, and randomized to treatment or standard care. The CTR program will consist of up to 40 h (8 weeks) of individual treatment based on memory, attention, executive functions, and visuospatial tasks to be autonomously performed with a tablet. The study outcomes will be evaluated at 6-month follow-up visit and will include the diagnosis of cognitive impairment, activities of daily living, quality of life, changes in frailty status and cognitive efficiency.

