**Figure 1 F1:**
[figure not shown]
CIPS-TER study experimental design.

The study is carried out at the Stroke Unit of Careggi University Hospital and at General Rehabilitation Unit of IRCCS Don Carlo Gnocchi in Florence, in accordance with the Helsinki Declaration. The study was approved by Local Ethics Committee (25546_spe) and each patient gave a written informed consent.

Patients included in the study were diagnosed with either ischemic or hemorrhagic stroke, regardless of lesion site. Neuroimaging was used to confirm diagnosis.

The study aims at estimating the incidence of post-stroke cognitive impairment in the short and mid-term, and at investigating the efficacy of a CTR program in reducing the risk of CI 6 months after stroke, the generalizability of cognitive training to real life and the impact on cognitive performances. It also aims at evaluating the effect of cognitive training on real-life activities (independence in daily living and quality of life). In the treated group, feasibility, adherence and appreciation of the CTR will also be evaluated.

Inclusion criteria of the study are: ischemic or hemorrhagic stroke (within 5–21 days after onset); age >18 years; evidence of impairment in global cognitive efficiency; NIHSS motor arm item = 0 in at least one arm; fluid Italian speaking; ability and willingness to sign informed consent.

Exclusion criteria are: normal cognitive functioning; pre-existing dementia; severe aphasia; motor deficits in both upper limbs; visual deficits.

All participants diagnosed with ischemic/hemorrhagic stroke are assessed within 5–21 days from onset. Table 1 shows the type of information collected and the instruments applied. Clinical information is retrieved from the clinical records; instruments are administered to patients and caregivers.

**Table 1 T1:** Data collected for screening and baseline evaluation and types of instruments used.

**Study phase**		**Data collection and instruments**
Screening Evaluation	Stroke severity	• NIHSS^*^
	Global cognitive efficiency	• Montreal cognitive assessment (MoCA)^*^ (Nasreddine et al., 2005)
	Verbal comprehension ability	• Token Test in those patients with 1 or 2 at NIHSS language item^*^ (Renzi and Faglioni, 1975)
	Pre-existing cognitive impairment	• Informant questionnaire on cognitive decline in the elderly (IQ-Code)^#^ (Jorm, 2004; van Nieuwkerk et al., 2021)

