# Caregiver interview.

For each patient, a caregiver or informant is identified and interviewed to assess the premorbid status. Cognitive premorbid status is evaluated by means of the informant questionnaire on cognitive decline in the elderly (IQ-Code) short form (16 items). IQ-Code explores the changes in daily activities requiring memory and other cognitive abilities observed over the last 10 years. An excellent accuracy of the IQ-CODE for detecting pre-existing dementia in transient ischemic attack and stroke was recently found for an optimal cut-off of >3.48 in a large longitudinal population-based study (Jorm, 2004; van Nieuwkerk et al., 2021). To assess severity of aphasia, we use the language item of the NIHSS according to the following criteria: if the score is 3, the patient is excluded. If the score is 1 or 2, we assess reading capabilities and comprehension. For this latter, we use the Token test (Renzi and Faglioni, 1975), excluding patients with an adjusted score below the 5th centile of the normal population. To be included, patients need to be able to use the tablet autonomously. For this purpose, we exclude patients with severe visual and hearing deficits and those not able to move at least one arm (motor item = 0 in at least 1 arm, not necessarily the dominant one).

Cognitive performances at this stage are assessed by means of Montreal Cognitive Assessment (MoCA). MoCA is a 30-point test recommended by the harmonization standards for the diagnosis and assessment of patients with vascular cognitive impairment, and it covers eight cognitive domains: verbal memory, visuospatial abilities, executive functions, attention, concentration, working memory, language, and orientation to time and place (Nasreddine et al., 2005). The predictive value of MoCA in the acute phase of stroke on the diagnosis of mid-term cognitive impairment is the topic of a previous publication from the proponents (Salvadori et al., 2013). MoCA is a good predictor of mid-term PSCI, independent of other clinical, neurological, and functional characteristics, and a cut-off of 21 is found to have good sensitivity (91%), specificity (76%), positive predictive value (80%), and negative predictive value (89%).

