At baseline, patients undergo a cognitive and mood assessment to investigate: neglect (star cancellation test; Halligan and Robertson, 2000; Wilson et al., 1987), apraxia (ideomotor apraxia test; Spinnler and Tognoni, 1987), fragility [Tilburg Frailty Indicator—TFI (Gobbens and Uchmanowicz, 2021; Mulasso et al., 2016) and Fried criteria (Fried et al., 2001) with IPAQ (Mannocci et al., 2010)] and cognitive reserve (CRI Questionnaire; Nucci et al., 2012). At 7 days after discharge, a telephone interview is conducted to investigate: functional state (ADL, IADL, and mRS; Katz et al., 1963; Lawton and Brody, 1969), quality of life [Stroke adapted sickness impact profile—SA-SIP (Buck et al., 2000) and EuroQol (Dorman et al., 1998)] and mood (CES-D; Lau et al., 2023).

During hospitalization, the caregiver interview involves the investigation of the patient's premorbid functional state (ADL and IADL; Katz et al., 1963; Lawton and Brody, 1969) and the possible presence of cognitive decline before stroke (IQ-Code; Jorm, 2004; van Nieuwkerk et al., 2021).

Stratified block randomization is used to assign participants to the experimental (tele-rehabilitation) or control group (standard care). This method ensures an even distribution of participants across predefined strata and minimizes imbalance in group sizes over time. Participants are stratified based on age, sex, NIHSS and MoCA scores. These variables were selected due to their potential influence on the study outcomes. Blocks of fixed size were generated to ensure that the number of participants in each group remained balanced throughout the enrollment process.

Randomization sequences were created using a computer-based random allocation software by the researchers of the Institute of Neuroscience (Florence) of the Italian National Research Council, who were not involved in participant recruitment or data collection and were in charge of the centralized randomization procedure. To prevent selection bias, randomization sequences are concealed from field workers.

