Experimental group: the cognitive telerehabilitation program is based on a medical device, with EU declaration of conformity. The product includes a central workstation, located in the clinic. From the central workstation, an expert psychologist ([name]), follows patients' performances and weekly adapts the difficulty of the tasks according to patients' performances. During the 2-month treatment, patients' compliance to the training sessions will be recorded.

Each patient randomized in the experimental group receives a tablet for the telerehabilitation program. This foresees sessions of telerehabilitation for 60 min per day, for 5 days a week, for a total of 8 weeks (totally making 40 h of individual treatment). Exercises are meant to work on the main cognitive domains: memory, language, attention, executive functions, visual-spatial and praxis skills. The daily treatment session includes 10-min exercises for each of the six cognitive domains.

Control group (standard care): participants are instructed to have a normal lifestyle and receive conventional treatments based on clinical indications provided by their referring physicians.

Two months after enrollment, at the end of the treatment session, a phone interview will be conducted to investigate satisfaction and gratification regarding CTR.

The endpoints of the study are to detect cognitive deficits in acute post-stroke phase and measure the impact these deficits might have on functional autonomy and quality of life of patients 6 months after stroke. The primary outcome will be the diagnosis of cognitive impairment, including mild cognitive impairment (MCI) and dementia according to the DSM-5 criteria for the diagnosis of mild or major neurocognitive disorders, respectively (American Psychiatric Association, 2022). Secondary endpoints will include assessment of functional status in daily life, quality of life, frailty and cognitive efficiency.

As shown in Table 2, the 6-month follow-up includes a neurological assessment with updates of clinical information, neurological exam and functional evaluation (NIHSS and mRS). Cognitive performances will be assessed by means of a comprehensive multidomain neuropsychological battery. The medical doctor and the neuropsychologist who will perform the follow-up visit will be blinded to treatment group.

**Table 2 T2:** Data collected for the 6-month follow-up visit with types of instruments used.

**Cognitive domain**	**Test**

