The neuropsychological battery will include test to assess global cognitive efficiency (MoCA alternative version; Siciliano et al., 2019), verbal and visual memory [Rey's Auditory Verbal Learning Test—RAVLT (Carlesimo et al., 1996), the Short Story test (Novelli et al., 1986) and Rey-Osterrieth complex figure Delayed-Recall—ROCF DR (Caffarra et al., 2002a)], constructional praxis, spatial planning skills, visual-spatial skills [ROCF copy (Caffarra et al., 2002a)], attention and executive functions [Trail Making Test (Giovagnoli et al., 1996), Visual Search (Della Sala et al., 1992), Symbol Digit Modalities Test (Nocentini et al., 2006) and Color Word Stroop Test (Caffarra et al., 2002b)], language [phonemic and semantic verbal fluency (Costa et al., 2014)], Premorbid Intelligence—IQ (Brief intelligence test—TIB; Colombo et al., 2002), quality of life [SA-SIP (Buck et al., 2000) and EuroQol scale (Dorman et al., 1998)], mood (CES-D; Lau et al., 2023), frailty [Fried criteria (Fried et al., 2001), with IPAQ (Mannocci et al., 2010) and Tilburg Frailty Indicator—TFI (Gobbens and Uchmanowicz, 2021; Mulasso et al., 2016)] and functional status (ADL and IADL; Katz et al., 1963; Lawton and Brody, 1969). Neglect, apraxia and verbal understanding are investigated with the same tests that are included in the baseline assessment.

The study protocol also includes an extensive telephone interview for all patients at the follow-up. By means of the phone interview data on global cognitive efficiency (Tele-GEMS; Montemurro et al., 2023), quality of life [SA-SIP (Buck et al., 2000) and EuroQol scale (Dorman et al., 1998)], mood (CES-D; Lau et al., 2023), frailty [IPAQ (Mannocci et al., 2010) and Tilburg Frailty Indicator—TFI (Gobbens and Uchmanowicz, 2021; Mulasso et al., 2016)], and functional status (ADL and IADL; Katz et al., 1963; Lawton and Brody, 1969) will be collected.

The diagnosis of major and minor neurocognitive disorder will be based on the available clinical assessment, i.e., patients who are not present at the outpatient visit will be classified based on the telephone interview.

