1) Effectiveness in Reducing Persistent Cognitive Impairment: The efficacy of the telerehabilitation program in reducing the incidence of persistent cognitive impairment at 6 months will be assessed using a chi-square test to compare proportions between groups.2) Impact on Daily Life Abilities: The effectiveness of the telerehabilitation program in improving patients' functional outcomes will be evaluated through within-group (pre-post) and between-group comparisons. Dependent variables will include functional independence measures, quality-of-life scores, changes in frailty status, and cognitive performance metrics.3) Predictors of Effectiveness of the telerehabilitation program: Multivariate regression models will be used to identify predictors of telerehabilitation efficacy. Covariates will include demographics (age, sex), cognitive resilience, baseline cognitive and functional abilities, TFI score, index stroke severity, and pre-existing brain structural changes.

The enrolment activities began in April 2024 and are ongoing. Since then, consecutive patients admitted with a diagnosis of ischemic or hemorrhagic stroke are being evaluated for participation in the study.

The flow-chart of the study is shown in Figure 2.

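### Objective 2 plans pre-post comparison of cognitive performance, but 12 of the 16 in-person cognitive scores have no pre-treatment value, and within-arm change in the others mixes treatment with recovery

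*Protocol article*

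**What the plan says.** Objective 2 in the Statistical analysis section concerns the effect of telerehabilitation on daily life abilities. It "will be evaluated through within-group (pre-post) and between-group comparisons", and the next sentence reads "Dependent variables will include functional independence measures, quality-of-life scores, changes in frailty status, and cognitive performance metrics". The variables form one list, with no split between those analysed as change and those compared only at follow-up. The Abstract's outcome list ends with "changes in frailty status and cognitive efficiency", which can be read as change in both.

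The assessment schedule is given test by test.

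- **Screening (Table 1 and the Methods text after it):** "Cognitive performances at this stage are assessed by means of Montreal Cognitive Assessment (MoCA". Table 1 adds "Token Test in those patients with 1 or 2 at NIHSS language item".
- **Baseline (Methods and Table 1):** "At baseline, patients undergo a cognitive and mood assessment to investigate: neglect", by star cancellation, and apraxia, by the ideomotor apraxia test. The remaining baseline instruments cover frailty, cognitive reserve and premorbid function.
- **6 months (Methods and Table 2):** "Cognitive performances will be assessed by means of a comprehensive multidomain neuropsychological battery". The text after Table 2 adds that "Neglect, apraxia and verbal understanding are investigated with the same tests that are included in the baseline assessment", and that MoCA is given in an alternative version.

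Patients who miss the 6-month visit are followed by telephone, where the global cognitive measure is Tele-GEMS.

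**The concern.** A pre-post comparison needs the same measure before and after treatment. Most of the follow-up battery is given once. For those scores the planned within-group analysis cannot be run, and the plan does not say what replaces it. The gap falls on domains that the programme trains: memory, attention, executive functions, visuospatial skills and verbal fluency.

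There is a second difficulty where a baseline does exist. Patients enter 5 to 21 days after stroke and are reassessed at 6 months. The Discussion accepts that improvement over this period may partly be natural recovery, and says that the longitudinal evaluation will clarify the matter. A within-arm change cannot do that; only the contrast between arms can.

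The risk is that the cognitive measures showing change are picked after the data are seen, or that change in the treated arm alone is reported as evidence of effectiveness.

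**Working it through.** No stated figure needs reproducing: the point rests on the schedule and not on the sample size. The check matches each cognitive test in Table 2 with Table 1 and the Methods text on screening and baseline.

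**Step 1: define the set.** Table 2 has 18 cognitive entries. Leave out Tele-GEMS (telephone only) and the Brief Intelligence test (premorbid intelligence, not an outcome): 18 − 2 = 16 in-person outcome scores.

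**Step 2: look for a pre-treatment value.**

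| Table 2 domain | Scores | Baseline in all | Baseline in a subset | No baseline |
|---|---|---|---|---|
| Global: MoCA | 1 | 1 | 0 | 0 |
| Memory: RAVLT immediate, RAVLT delayed, Short Story, ROCF recall | 4 | 0 | 0 | 4 |
| Constructional and visuospatial: ROCF copy | 1 | 0 | 0 | 1 |
| Attention and executive: Trail Making A and B, Visual Search, SDMT, Stroop | 5 | 0 | 0 | 5 |
| Language: phonemic fluency, semantic fluency, Token Test | 3 | 0 | 1 | 2 |
| Neglect: star cancellation | 1 | 1 | 0 | 0 |
| Apraxia: ideomotor apraxia test | 1 | 1 | 0 | 0 |
| **Total** | **16** | **3** | **1** | **12** |

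Thus 12/16 = 75% have no pre-treatment value. Three have one in all patients. The Token Test has one only in patients with NIHSS language item 1 or 2, and those whose adjusted score falls below the 5th centile are excluded, so this is a selected group.

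**Step 3: what within-arm change estimates.** Let r be the mean spontaneous recovery to 6 months and t the treatment effect.

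- Change in the treated arm: r + t
- Change in the control arm: r
- Difference between arms: (r + t) − r = t

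A pre-post test in the treated arm can be significant with t = 0 whenever r is not zero. The between-arm difference removes r, and it needs no baseline to be valid under randomization.

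**Step 4: what a baseline adds to the between-arm comparison.** Let ρ be the correlation between the baseline covariate and the 6-month score. Relative to an unadjusted 6-month comparison (variance 1), the variance is 1 − ρ² with baseline adjustment. For a change score, with equal SDs at both visits, it is 2(1 − ρ). The documents give no ρ, so the range is an assumption.

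| ρ | Adjusted: 1 − ρ² | Change score: 2(1 − ρ) |
|---|---|---|
| 0.3 | 0.91 | 1.40 |
| 0.5 | 0.75 | 1.00 |
| 0.7 | 0.51 | 0.60 |

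The gap is 2(1 − ρ) − (1 − ρ²) = (1 − ρ)², which is never negative. Adjustment is therefore at least as precise as comparing changes. It also works for scores without their own baseline, using MoCA total as the covariate.

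**The case against.** The strongest reply is that objective 2 names two kinds of comparison and need not mean that every variable receives both. Only frailty is worded there as a change, so pre-post may be intended only where a baseline exists. The secondary endpoint is cognitive efficiency, which both tables attach to MoCA, and detailed allocation of analyses is commonly left to a fuller document. This reading is possible, but the article does not state it. The article does give both schedules and the analysis, and as written they do not fit. Nor does the charitable reading meet the second difficulty, that pre-post change is offered as a way of evaluating effectiveness.

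Several stronger conclusions that a reader might draw do not stand.

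- **That the effect on cognition cannot be assessed.** It can: the planned between-group comparison is valid at 6 months for every score.
- **That there is no domain-level baseline.** MoCA domain scores are used for eligibility and give a coarse one for several trained domains.
- **That the sentence on shared tests is wrong.** It names the instrument used at both times, and the Token Test is in Table 1. It does not claim that every patient had it at baseline.
- **That the alternative MoCA version biases results.** An alternative form is a usual guard against practice effects and applies to both arms. The document does not show that the forms differ.

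**Conclusion.** The point holds in a limited form. The planned pre-post comparison cannot be made for 12 of 16 in-person cognitive scores, and for one more (the Token Test) only in a selected subset. For the three with a baseline in all patients, within-arm change does not separate treatment from recovery. The chi-square comparison of the 6-month diagnosis, which is the primary analysis, is untouched, as is the validity of the between-group part of objective 2.

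The count assumes that cognitive performance metrics include the Table 2 battery; the article does not define the term. If only MoCA were meant, the missing-baseline part would fall away and the recovery part would remain. The size of any misleading within-arm change cannot be computed, because the document gives no recovery rate or standard deviation.

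**What to change.** In objective 2, base effectiveness on the between-arm comparison and separate the cognitive variables:

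1. For the 12 battery scores without a baseline and for the Token Test, compare arms at 6 months, adjusted for baseline MoCA total. MoCA is collected in all patients at screening and is already a stratification factor.
2. For MoCA, star cancellation and ideomotor apraxia, compare arms at 6 months, adjusted for the baseline value of the same measure.
3. Report within-arm pre-post change, where it exists, as descriptive only.
4. State that patients followed only by telephone have Tele-GEMS but no battery and no 6-month MoCA, and so do not contribute to these scores.

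This changes analysis wording and adds no assessment. The article describes enrolment as ongoing, so the change can be fixed before the outcome analysis. The downside is small: the battery scores cannot be reported as improvement from baseline, only as differences between arms.

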### Statistical analysis

The sample size was determined a priori based on data reported in previous studies and reviews on cognitive rehabilitation, along with feasibility and logistical considerations. These included the actual flow of stroke patients admitted to Careggi University Hospital and the Intensive Rehabilitation Unit of IRCCS Don Gnocchi during the planned 12-month enrollment period, along with the availability of dedicated spaces, appropriate settings, and personnel.

Yearly, ~400 stroke patients are admitted to the Stroke Unit of Careggi University Hospital, and ~130 patients are referred to the Intensive Rehabilitation Unit of IRCCS Don Gnocchi. Based on an estimated screening pool of ~550 patients during an enrolment period of 12 months, and accounting for an expected frequency of cognitive deficits in 75% of stroke patients during acute phase (enrolment period), as well as a substantial proportion of ineligible patients and refusals, we estimate to enroll ~100 patients. Eligible patients will be randomized in a 1:1 ratio: 50 will be allocated to the experimental group receiving the telerehabilitation program and 50 to the control group receiving standard care. Both groups will be balanced for key demographic and clinical characteristics. This sample size was determined based on pilot studies and a power analysis to ensure a statistical power of 80% to detect significant differences between the two groups assuming a two-sided alpha level of 0.05.

The data management system will include automatized procedures of data analysis. Specifically, independent sample *t*-tests and chi square tests will be used to compare demographics, vascular risk factors, and global cognitive and functional status, and the results will be available in real time during the whole enrollment period. Stratified block randomization will be employed to balance potential prognostic factors—such as age, gender, MoCA scores, and NIHSS scores—across the two groups, minimizing confounding and enhancing internal validity.

At the conclusion of the 6-month follow-up, primary and secondary outcome analyses will be conducted using SPSS version 28. The analysis will focus on three main objectives:

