## Discussion

Post-stroke cognitive impairment is a very common complication. Available epidemiological data report that about 75% of stroke patients experience cognitive worsening in the acute phase, which for many patients may persist in the medium to long term. These early forms of cognitive impairment could benefit from specific treatments (Ye et al., 2022). In this setting, a randomized controlled clinical trial to evaluate the effectiveness of telerehabilitation could expand knowledge and might bring evidence on feasibility in the acute stroke setting, cost-effectiveness, usability of delivery technologies, and, most importantly, help in the identification of the ideal type of patient who may benefit from such treatment. CIPSTER has been designed with these purposes.

Cognitive rehabilitation interventions focus on restorative and compensatory strategies that aim to restore cognitive function through repeated practice, develop new behaviors to compensate for cognitive deficits, and adapt to these cognitive deficits by reducing the effects of cognitive impairment on functional ability using strategies that minimize demands on attention skills. Post-stroke cognitive rehabilitation interventions have shown some benefits, but evidence is generally limited. Evidence from Cochrane showed that the effectiveness of cognitive rehabilitation for cognitive deficits following stroke remains to be confirmed (Chung et al., 2013; Loetscher et al., 2019; das Nair et al., 2016). Cognitive rehabilitation may improve some specific aspects of attention or executive functions immediately after treatment, but there is no evidence on the persistence of benefits. Improvements after cognitive rehabilitation are often limited, short-term, and dependent on various factors, such as severity of injury, timing of intervention, and type of treatment approach. It is also important to emphasize that tailoring interventions to patients' individual needs is critical to achieve more effective outcomes.

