The results of CIPS-TER study may thus contribute to the knowledge on the effects of an early cognitive telerehabilitation on the reduction of persistent cognitive and functional burden in stroke patients, and thus on the potential benefits of including cognitive telerehabilitation as an effective component of post-stroke care pathways after discharge from inpatient care. In line with precision medicine, CIPS-TER project could also help to highlight which clinical features characterize stroke patients who could maximally benefit of such cognitive interventions. Finally, experiences and setups gathered within CIPS-TER project could represent a technical and methodological background for future studies aimed at the development and/or the evaluation of cognitive telerehabilitation systems in stroke patients.

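### Objective 3 seeks predictors of who benefits from telerehabilitation, but lists only baseline covariates, with no arm term and no arm-by-covariate interaction; as listed, it finds prognostic factors

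*Protocol article*

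**What the plan says.** The Statistical analysis section of the protocol article gives three main objectives. For the third: "Multivariate regression models will be used to identify predictors of telerehabilitation efficacy". The terms follow: "Covariates will include demographics (age, sex), cognitive resilience, baseline cognitive and functional abilities, TFI score, index stroke severity, and pre-existing brain structural changes". No outcome is named for this objective. The text does not say whether one or both arms enter the model, and the list contains neither randomised group nor a product of group with any covariate. Nowhere does the article mention an interaction, moderator or subgroup test.

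The Discussion says how the result is to be used. The trial should "help in the identification of the ideal type of patient who may benefit from such treatment", and the project could "help to highlight which clinical features characterize stroke patients who could maximally benefit of such cognitive interventions".

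The Statistical analysis section also says that stratified randomisation is meant to "balance potential prognostic factors—such as age, gender, MoCA scores, and NIHSS scores—across the two groups". Age, sex, baseline cognition and stroke severity are thus called prognostic there and reappear under objective 3 as candidate predictors of efficacy.

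**The concern.** Benefit from the programme is a difference between arms. A factor predicts benefit only if that difference changes with the factor, which is an arm-by-covariate interaction. A covariate coefficient estimated without that term says who has a good or bad six-month outcome. In the treated arm alone it mixes natural recovery with any treatment effect. In the pooled data it averages over the arms.

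The Discussion itself warns that gains at six months may partly reflect spontaneous recovery. A covariate-only model has exactly this weakness: it would credit the programme with recovery that younger or less severely affected patients would have had anyway. What is at stake is the secondary conclusion about whom to treat. The primary comparison of proportions is not affected.

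**Working it through.** **1. The plan's own figure.** The article states no figure for objective 3. Its only design figure is the sample size: "50 will be allocated to the experimental group receiving the telerehabilitation program and 50 to the control group receiving standard care", said to give "a statistical power of 80% to detect significant differences between the two groups assuming a two-sided alpha level of 0.05". It gives no effect size, control rate or dropout rate, so this cannot be reproduced, only inverted. For the primary outcome, which "will be assessed using a chi-square test to compare proportions between groups", the usual two-proportion formula without continuity correction gives 80% power at 50 per arm for 50% v 23.3%, a difference of 26.7 points. Over control rates of 40% to 80% the detectable difference is about 25 to 28 points. This is used in step 4.

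**2. What each model estimates.** Let T be arm (0/1), x a baseline covariate and p the risk of impairment.

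- Treated only: logit p = a + b·x. Here b is the prognostic slope in treated patients; there is no comparison with control.
- Pooled main effects: logit p = a + c·T + b·x. Here b is a slope common to both arms. Adding arm alone does not help.
- Interaction: logit p = a + c·T + b·x + d·T·x. Here d is the change in treatment effect per unit of x, the only term that addresses who benefits.

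**3. How often a purely prognostic factor is flagged.** Simulated trials had 50 per arm, one standard-normal covariate, true d = 0 and two-sided p < 0.05. The control risk at the covariate mean was 50%, which is an assumption; the Background gives about 50% for medium- to long-term impairment. Covariate strength and treatment effect are also assumptions. The first three rows use treatment log-odds -0.85 and 3,000 runs each; the last three use -0.8 and 2,000 runs each.

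| Covariate effect per SD | Treated only | Pooled main effects | Interaction test |
|---|---|---|---|
| OR 1.5 (log-odds 0.41) | 22% | 47% | 5% |
| OR 2.0 (0.69) | 52% | 88% | 5% |
| OR 2.5 (0.92) | 75% | 98% | 4% |
| log-odds 0.5 | 31% | 62% | 5% |
| log-odds 1.0 | 82% | 99% | 4% |
| log-odds 1.5 | 97% | 100% | 4% |

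With no treatment effect at all, the OR 1.5, 2.0 and 2.5 scenarios give 26%, 59% and 81% treated-only, 49%, 89% and 98% pooled, and 4-5% for the interaction test. Repeat runs agree within simulation error, so the overall ranges are about 22-98%, 47-100% and 3-6%.

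**4. What the interaction test can detect.** Take a balanced binary modifier, four cells of 25 and risks near 0.5. The standard error of the difference in risk differences is √(4 × 0.25/25) = 0.20. Power is approximately Φ(D/0.20 − 1.96):

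- D = 0.27 (as large as the detectable main effect): Φ(1.35 − 1.96) = 27%
- D = 0.40: Φ(2.00 − 1.96) = 52%
- D = 0.54: Φ(2.70 − 1.96) = 77%

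**The case against.** The article is a condensed text. It speaks of models in the plural, gives an open list of covariates and never says main effects only. Under objective 1 efficacy is a between-group comparison, so predictors of efficacy can be read as effect modifiers. The full protocol or an analysis plan may contain the interaction terms. This stands: the article does not exclude interactions, and the risk is conditional on fitting the model as listed.

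A reader might also infer that the regression is confined to the roughly 50 treated patients, and go on to count too few events for at least eight terms. The text does not support that. Where the authors restrict an aim to the treated group (feasibility, adherence, appreciation) they say so, and they do not for objective 3. Nor is a binary outcome stated for it; objective 2 lists several scores. No events-per-term figure is therefore claimed.

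The simulation uses one covariate and assumed strengths, whereas the plan is multivariable. The upper end of the range needs an odds ratio of about 4.5 per SD (exp 1.5). The percentages illustrate the risk and do not forecast this trial. The Discussion's wording is also tentative, and it concedes limited power.

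What the objection does not remove is the mismatch. The article names the method, the covariates and the interpretation of a main objective, and these three do not fit together. Which quantity answers the question is more than modelling detail.

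**Conclusion.** The point holds in conditional form. As listed, the objective 3 model answers a prognostic question while the Discussion asks who benefits. If it is fitted that way, a factor with no bearing on the treatment effect is flagged in about 22-98% of treated-only fits or 47-100% of pooled fits, against about 3-6% with an interaction test. These ranges rest on assumed covariate log-odds of 0.4 to 1.5 per SD, a 50% control risk, treatment log-odds of about -0.8 (or none) and 50 per arm without dropout. The qualitative conclusion does not depend on them.

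It would go too far to say that the trial plans to exclude interactions, or that it will name as ideal patients those who would have recovered anyway. The documents state neither. This should be corrected before the analysis; it does not threaten the primary result.

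**What to change.** State that objective 3 is analysed in all randomised patients, with arm, covariate and arm-by-covariate terms, for a small prespecified set of baseline modifiers kept continuous. Baseline MoCA, NIHSS and cognitive reserve are possible examples; the choice is the investigators'. Name the outcome. Report each interaction estimate with its 95% CI, labelled exploratory. Call any model without interactions an analysis of prognostic factors.

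The cost is wording only: the covariates are already listed for collection, and enrolment is unaffected. The real downside is precision. With 100 patients, power is about 27% for an interaction as large as the detectable main effect, so a non-significant interaction will not show that a factor is irrelevant. The Discussion's statements about ideal patients should be toned down to match.
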